## Abstract

**Background:**

Leadership is a valuable skill that can be taught in school, and which may have benefits within and beyond the classroom. Learning to Lead (L2L) is a student-led, primary school-based leadership program whereby older ‘*peer leaders’* deliver a fundamental movement skills (FMS) program to younger ‘*peers’* within their own school.

**Aim:**

The aims of the study are to determine the efficacy of a peer-led FMS intervention on: (i) *peer leaders’* (aged 10 to 12 years) leadership effectiveness (primary outcome), leadership self-efficacy, well-being, and time on-task in the classroom; (ii) *peers’* (aged 8 to 10 years) physical activity levels, actual and perceived FMS competency, cardiorespiratory fitness, muscular power, and executive functioning; and (iii) teachers’ (referred to as ‘*school champions*’) work-related stress and well-being.

**Method:**

L2L will be evaluated using a two-arm parallel group cluster randomised controlled trial. Twenty schools located within a two-hour drive of the University of Newcastle, Australia will be recruited. We will recruit 80 students (40 *peer leaders* and 40 *peers*) from each school (*N* = 1,600). L2L will be implemented in three phases: Phase 1 –*school champions’* training via a professional learning workshop; Phase 2 –*school champions’* delivery of leadership lessons to the *peer leaders*; and Phase 3 –*peer leaders’* delivery of the FMS program to their younger *peers*. The FMS program, consisting of 12 x 30-minute lessons, will be delivered over the course of one school term (10 weeks). Study outcomes will be assessed at baseline (between mid-March to June, Terms 1 and 2), intervention end (mid-August to September, Term 3), and follow-up (November to mid-December, Term 4. This trial was prospectively registered on the Australian New Zealand Clinical Trials Registry (ANZCTR); registration number: ACTRN12621000376842.

## Introduction

‘Leadership’ refers to the behavioural processes through which an individual influences others toward achieving specific goals or objectives [1], and is a valuable life skill that can be developed in the school setting. Providing children with opportunities to develop their leadership skills has been shown to improve their academic outcomes [2], increase their likelihood to take initiative in the classroom [2], and may improve learning autonomy (e.g., studying, completing homework, reviewing lessons etc) [3]. Improving leadership skills at school may also transfer to non-school settings and other life stages (e.g., employment in early adulthood). Surprisingly, there have been very few school-based programs focussed on developing students’ leadership ability. Further, previous peer-led programs have predominantly focused on the benefits for those being led (i.e., *peers*) [4–6], rather than exploring benefits for the *leaders* themselves.

Schools have been identified as key settings for physical activity promotion in children and adolescents [7]. Participating in moderate-to-vigorous intensity physical activity (MVPA) is vital for children’s physical, social, psychological, and cognitive development [8, 9]. Concerningly, less than 20% of Australian children are sufficiently active [10]. Additionally, many children finish primary school without mastering important fundamental movement skills (FMS); e.g., throwing, catching, running, and kicking [10]. While schools are an ideal environment to target children’s physical activity and movement skills, the effects of such interventions are typically modest [11]. The average effect of school-based physical activity interventions on objectively measured MVPA is less than two minutes per day [12]. Further, when interventions are scaled-up, they often experience significant ‘voltage drop’ [13–15]. For example, a 2021 systematic review found that when physical activity interventions are scaled-up, they typically achieve less than 60% of their pre-scale effect size [16]. School-based physical activity interventions can be challenging to implement [17], the problems of which are further compounded when teachers lack the necessary competencies, time, and support to enable effective program delivery [18]. Accordingly, schools require physical activity interventions that are both effective and scalable.

Australian teachers report high levels of work-related stress and burnout [19]. Sources of stress for school teachers include managing student discipline, high workloads, poor working conditions, and lack of support from school administrators [20, 21]. A recent study of Australian teachers (*N* = 960) concluded that improving measures for managing student behaviour was among teachers’ top priorities to improve their own well-being [22]. In line with this, negative student-teacher relationships are associated with lower occupational well-being among teachers [23]. Providing students with opportunities to develop their leadership skills may help to manage their behaviour within and beyond the classroom. This may improve the relationship with their teacher, mitigating teacher stress and improving teacher well-being.

We conducted a pilot study to evaluate a school-based peer leadership program in two primary schools in New South Wales (NSW), Australia (N = 224 students) [24]. The intervention resulted in large improvements in *peer leaders’* effectiveness (*d* = 1.09) and *peers’* FMS competency (*d* = 0.95). Importantly, the program was well received by teachers and students, increasing the likelihood of program dissemination. Although classroom behaviour was not formally measured, teachers anecdotally reported improvements in students’ classroom behaviour following participation in our leadership program. Despite these positive findings, the pilot study involved a quasi-experimental design in two schools and our findings need to be confirmed using a robust cluster randomised controlled trial (RCT).

Previous investigations have demonstrated that peer leadership programs can have a range of benefits for those being led, such as improvements in physical activity [25], mathematical ability [26], and nutrition knowledge [6]. The current project builds upon the findings of our previous pilot study and will examine the effects of a student-led, school-based leadership program known as Learning to Lead (L2L) on students’ behavioural, psychological, and cognitive outcomes. In Australia, students in their last two years of primary school are referred to as Stage 3 students and are typically between the ages of 10 and 12. Henceforth, these students will be referred to as *‘peer leaders’*. Students in the preceding two years of schooling are referred to as Stage 2 students and are typically between the ages of 8 and 10. These students will be referred to as ‘*peers’*. The primary aim is to determine the impact of L2L on *peer leaders’* leadership effectiveness. The secondary aims are to determine the impact of L2L on i) *peer leaders’* self-reported leadership effectiveness, leadership self-efficacy, well-being, and time on-task in the classroom; ii) *peers’* physical activity levels, executive functioning, health-related fitness, and actual and perceived FMS competency; and (iii) teachers’ work-related stress and well-being. We will also examine whether changes in FMS competency mediate changes in executive functioning. Further, this study will be the first to test the hypothesis that improving children’s leadership skills may have ‘spill over’ effects for leaders’ time ‘on-task’ in the classroom and teachers’ work-related stress and well-being.

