## Materials and methods

### Research design

L2L will be evaluated using a two-arm parallel group cluster RCT. Schools will be randomly allocated to a group by an independent researcher via a computer-based random number generator to either an intervention or wait-list control. In Australia, the school year is divided into four terms, each approximately 10 weeks in duration. The study will be conducted across two cohorts (2022 and 2023), with assessments at baseline (between mid-March to June, Terms 1 and 2), intervention end (mid-August to September, Term 3), and follow-up (November to mid-December, Term 4). See Fig 1 for the SPIRIT Schedule Of Enrolment, Interventions, And Assessments. The trial has been prospectively registered with the Australian New Zealand Clinical Trials Registry (registration number: ACTRN12621000376842). The design, conduct and reporting will adhere to CONSORT (Consolidated Standards of Reporting Trials) [27] and TIDieR (Template for Intervention Description and Replication) [28] checklists. The trial has been approved by the University of Newcastle’s ethics committee (reference number: H-2020-0109) and the NSW Department of Education’s State Education Research Applications Process (SERAP; reference number: 2020143).

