### Control group

To prevent compensatory rivalry and resentful demoralisation, we will use a wait-list control group. Schools allocated to the control group in cohorts 1 and 2 will receive the program in Term 4 of 2022 and 2023, respectively.

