#### Secondary outcomes (*peers*)

Actual and perceived object control FMS competency, and health-related fitness will be assessed at baseline (Term 1: weeks 8–10 to Term 2), and intervention end (Term 3: weeks 5–10). Physical activity will be measured at baseline and mid-intervention:

*Actual FMS competency*. Will be assessed using a subset of object control skills (i.e., overarm throw, kick, and catch) from the Test of Gross Motor Development 3 [46]. Children will be filmed performing three trials (inclusive of one practice trial) of each of the three skills. These skills were selected due to their transferability into a variety of different sports that are popular among Australian children. Research assistants will assess the videos according to the performance criteria. Each skill component will be scored a “1” if observable and performed correctly or “0” if performed incorrectly. This procedure will be completed for each of the two main trials, and trial scores will be summed to calculate a total score for each skill. An overall object control movement skill score will be calculated by summing the skill scores.

*Perceived FMS competency*. Perceived competence in the same three fundamental movement skills described above will be assessed using the Pictorial Scale of Perceived Movement Skill Competence, which has demonstrated face validity and excellent test-retest reliability in young children [47].

*Physical activity during school hours*. Children will be asked to wear ActiGraph GT9X Link accelerometers on their non-dominant wrist during school hours for five school days. Accelerometers will be distributed at the start of each school day (i.e., 9:00am) and collected at the end of each school day (i.e., 3:00pm). Physical activity will be categorised into light, moderate and vigorous intensity using validated cut-points [48].

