*Cardiorespiratory fitness*. The 20m Multistage Fitness Test consists of one-minute stages of incremental speed running. Participants are required to run between two lines 20m apart whilst keeping up with the pace set by an audio recording. The test concludes upon voluntary exhaustion, or when they fail to reach the line concurrent with the audio signal on two successive occasions (warning provided by assessor). The participants are provided verbal encouragement during this test. Performance on this test has moderate-to-high criterion-related validity for estimating maximum oxygen uptake in children (r = 0.78, CI = 0.72 to 0.85) [49].

*Muscular power*. The Standing Long Jump Test requires the participant to stand behind a line and perform a maximal long jump–taking off and landing with two feet simultaneously. Participants perform two jumps, with the furthest jump recorded as the participants’ final score. This measure is associated with other lower body muscular fitness tests (R^2^ = .83 to .86) and with upper body muscular fitness tests (R^2^ = .69 to .85) in children [50], thus demonstrating its validity as a measure of overall muscular fitness in this population.

*Executive function*. Inhibition and task shifting will be assessed using two tests from the NIH Toolbox for the Assessment of Neurological and Behavioural Function (NIH-TB). Both tests are self-administered (not requiring administration by the researcher) and will be administered on an electronic tablet. For both tests, the versions designed for 8–11-year-old children will be used. The tests will be administered in groups, whereby up to 20 students will complete the tests on their tablets at the same time.

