### Statistical analysis

General linear mixed models using the ‘lme4’ package in R software [56] will be used to assess the impact of treatment (L2L or control), time (treated as categorical with levels baseline, intervention end and follow-up) and the group-by-time interaction. The primary endpoint of the study will be intervention end (Term 3: weeks 5–10). Our analyses will be adjusted for the clustering of effects at the class and school levels, using random intercepts. Our mediation analyses will use a full information maximum likelihood procedure in Mplus. To determine whether changes in *peer leaders’* on-task behaviour mediate the effect of the L2L program on teachers’ work-related stress and wellbeing, structural equation models will be used to test the following: (i) the total effect of the program on work-related stress and well-being (C pathways); (ii) the effect of the intervention on the mediators (A pathways); (iii) the mediator effects on teachers’ work-related stress and well-being (B pathways); (iv) the direct effect of the L2L on teachers’ work-related stress and well-being with the inclusion of mediators in the model (Cʹ pathways) and (v) the indirect effect of L2L on teachers’ work-related stress and well-being (AB pathways).

To determine whether changes in *peers’* fundamental movement skills mediate the effect of the L2L program on their executive functioning, structural equation models will be used to test: (i) the total effect of the program on executive functioning (C pathways), (ii) the effect of the program on the mediators (A pathways), (iii) the mediator effects on executive functioning (B pathways), (iv) the direct effect of the program on executive functioning with the inclusion of mediators (C’ pathways), and (v) the indirect effect of the program on executive functioning (AB pathways). As Mplus does not support bootstrapping with clustered data, single-level bootstrap confidence intervals will be compared with confidence intervals adjusted for clustering.

Data regarding schools’ exposure to potential sources of contamination (or co-intervention) will be assessed via items in school, teacher, and Principal surveys following the intervention period. Potential effects on outcomes will be explored via sensitivity analyses.

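### The FMS-to-executive-function mediation cannot show direction if both are measured at the same visits, and a Term 4 measurement would lose the untreated control

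*Protocol article*

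**What the plan says.** The aim, at the end of the Introduction, is directional: "We will also examine whether changes in FMS competency mediate changes in executive functioning".

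Under Secondary outcomes (peers), the timing sentence begins "Actual and perceived object control FMS competency, and health-related fitness will be assessed at baseline" and continues "and intervention end (Term 3: weeks 5–10). Physical activity will be measured at baseline and mid-intervention". FMS therefore has two measurements, and only physical activity has one during the intervention. Executive function is described in the same section ("Inhibition and task shifting will be assessed using two tests from the NIH Toolbox"), but the timing sentence does not name it and its own paragraphs give no visit times. The schedule is in Fig 1, which is not shown in the text at hand.

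A third time point exists for the trial as a whole. Research design lists baseline, intervention end "and follow-up (November to mid-December, Term 4", and the mixed model under Statistical analysis has "time (treated as categorical with levels baseline, intervention end and follow-up". The Control group section says that control schools "will receive the program in Term 4 of 2022 and 2023", which is the term of the follow-up.

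Statistical analysis sets out the mediation model path by path, in one direction only, including "iii) the mediator effects on executive functioning (B pathways" and the indirect effect AB.

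**The concern.** Randomisation protects the programme's effect on FMS (A) and its total effect on executive function (C). It does not protect B, because pupils are not randomised to their level of FMS. If both variables are taken at the same visits, B is the association between two changes over one interval. It fits equally well if better attention and inhibition help pupils to learn the skills, or if something unmeasured drives both.

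A significant AB would then be reported as mediation under the stated aim even when FMS does nothing to executive function. What is at stake is the answer to one secondary aim. The primary outcome and all randomised comparisons are unaffected.

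**Working it through.** The protocol gives no figure for the mediation analysis, so there is none to reproduce.

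**Timing, both branches**

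- Executive function at baseline and intervention end: mediator and outcome are concurrent, so there is no time order.
- Executive function in Term 4: the outcome comes after the mediator, but control schools receive the programme that term, so the contrast is no longer with untreated schools. Later measurement also does not remove a common cause.

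**Inputs**

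- From Sample size calculation: 20 schools, 40 peers per school and 10% loss, giving 40 × 0.9 = 36 analysed per school. The loss figure is stated for peer leaders and carried over to peers.
- ICC: 0.15 is stated, for leadership effectiveness only. None is given for FMS or executive function, so 0.05 and 0.15 were both used.
- Assumed, because the protocol gives none: programme effects a = 0.5 SD on FMS and c = 0.2 SD on executive function, and reverse slope r = 0.1, 0.2 or 0.3.

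**Expected size of the false indirect effect (concurrent branch)**

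Let EF = c·T + error and FMS = a·T + r·EF + error, with unit error variances and no path from FMS to EF. The planned model then estimates A = a + r·c and B = r/(1 + r²). The true indirect effect is 0.

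| r | A | B | AB | Share of C = 0.2 | Simulated mean AB |
|---|---|---|---|---|---|
| 0.1 | 0.5 + 0.02 = 0.52 | 0.1/1.01 = 0.099 | 0.051 | 26% | 0.052 |
| 0.2 | 0.5 + 0.04 = 0.54 | 0.2/1.04 = 0.192 | 0.104 | 52% | 0.102 |
| 0.3 | 0.5 + 0.06 = 0.56 | 0.3/1.09 = 0.275 | 0.154 | 77% | 0.152 |

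**How often the interval excludes zero**

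Simulated trials used cluster-robust standard errors and a Monte Carlo 95% interval for AB. Ranges span independent runs.

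| r | ICC 0.05 | ICC 0.15 |
|---|---|---|
| 0.1 | 71–77% | 43–45% |
| 0.2 | 98–99% | 78–81% |
| 0.3 | 99–100% | 82–85% |

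With no link between the two variables the rate is 6% and 5%, so the procedure is roughly calibrated and the excess comes from the reverse path. Adding baseline FMS and executive function as covariates (assumed stability 0.6) gives 68 / 99 / 100% at ICC 0.05 and 40 / 77 / 85% at 0.15. Baseline adjustment does not cure it.

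**Other mechanisms (600 runs each)**

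| Scenario | Expected AB | Interval excludes zero, ICC 0.05 / 0.15 |
|---|---|---|
| Reverse only: a = 0, c = 0.4, r = 0.3 | 0.12 × 0.275 = 0.033 | 15% / 11% |
| Reverse plus direct: a = 0.5, c = 0.4, r = 0.3 | 0.62 × 0.275 = 0.171 | 100% / 90% |
| Common cause, loadings 0.3, a = 0.5 | 0.5 × 0.09/1.09 = 0.041 | 55% / 33% |
| Common cause, loadings 0.4, a = 0.5 | 0.5 × 0.16/1.16 = 0.069 | 91% / 60% |
| True mediation: a = 0.5, FMS-to-EF slope 0.3 | 0.5 × 0.3 = 0.15 | 97% / 79% |

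True mediation (0.15) and reverse plus direct (0.17) give nearly the same estimate.

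**Can a threshold or a reverse model decide direction?**

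Given arm, the residual correlation is r/√(1 + r²) in the reverse model. With a true FMS-to-EF slope b it is b/√(1 + b²). At 0.3 both equal 0.3/√1.09 = 0.287. A rule that AB must survive a residual correlation of 0.3 refused about 65–67% of false and 59–67% of true effects at slope 0.3 and ICC 0.05. At slopes 0.1 and 0.2 it refused essentially all of both.

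A reverse model does no better. In the reverse-plus-direct case the wrong (forward) model gave AB 0.17 and was significant in 100% / 90% of runs. The right (reverse) model gave 0.12 and 90% / 62%.

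**The case against.** The strongest objection is about timing. A reader might infer that the protocol sets FMS and executive function over the same baseline to intervention-end interval. The documents do not support that as a stated fact. The timing sentence omits executive function, a Term 4 follow-up exists, and Fig 1 may settle the matter. This stands, so the same-visit problem is conditional. It does not rescue the aim, because the Term 4 branch has its own fault.

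Second, an unprotected B path is common to mediation analyses within a single trial, and an article may leave sensitivity analyses to a full protocol or SAP. This also stands in part: the absence of a sensitivity analysis from the article is not the finding. The finding is that the stated aim and the one-direction model support a claim that the described measurements cannot carry.

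Third, the false-positive rates rest on assumed effects. A reader might take 71–100% as this trial's error rate, which the documents do not support. Across the scenarios above that link the two variables without true mediation, the rate runs from 11% to 100%. The low end needs the programme to have no direct effect on FMS. That is not what it is designed for, and the Introduction reports d = 0.95 for FMS in the pilot.

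**Conclusion.** The concern holds in conditional form. FMS is measured only at baseline and intervention end, and the text does not fix the timing of executive function. If the two are concurrent, AB does not identify direction. A false indirect effect of about 0.05 to 0.15 SD can then appear, about a quarter to three quarters of an assumed 0.2 SD total effect. Its interval would exclude zero in 71–100% of trials at ICC 0.05 and 43–85% at ICC 0.15. If executive function is measured in Term 4, the comparison is no longer with untreated controls.

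The sizes depend on the assumed programme effects, reverse slopes and ICCs. Part of the risk is unmeasured confounding rather than reverse direction. The matter is worth correcting, but it concerns the interpretation of a secondary aim only.

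**What to change.** - In Statistical analysis, keep A and C as the randomised effects. Report AB with a sensitivity analysis: refit the model with a fixed residual correlation between FMS and executive function, and give the correlation at which AB becomes zero.
- In the Introduction, and in the eventual conclusion, word the result as an association between change in FMS and change in executive function, consistent with mediation only if there is no reverse or common-cause path.
- State in the text at which visits executive function is measured.
- Do not attach a pass/fail cut-off such as 0.3 to the residual correlation, since it rejects true and false mediation about equally. Do not use a reverse-direction model to decide direction.

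The cost is a few more model fits on data already collected and a small rewording. The downside is a less favourable mediation claim on a secondary aim.
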